**Summary of Research Proposal. [name] (33248)**

***Introduction.***

Aging is characterized by a loss of muscle (sarcopenia) and bone (osteopenia) mass. Strength exercise has been shown to increase muscle mass/strength and bone mass in older adults. We and others have found that short-term creatine monohydrate (CrM) supplementation can enhance the benefits from strength exercise training in older adults. We have recently found that conjugated linoleic acid (CLA, an essential fatty acid) increased bone mass in rats even when treated with corticosteroids. To date, the effects of CLA on muscle and bone, +/- CrM, has not been evaluated in sedentary or strength trained older adults. Together, CLA and CrM supplementation should complement each other’s beneficial effects on bone and muscle mass, respectively. The benefits of the CLA/CrM combination should be magnified with the additional stimulus of strength exercise training. Given the increase in the proportion of adults over the age of 65y, data from the current proposal could lead to the development of safe and relatively inexpensive interventions for sarcopenia and osteopenia.

## *Objectives.*

## To determine the pattern of gene expression in skeletal muscle in older adults in response to strength exercise training and nutritional interventions with CLA and creatine.

- To asses whether CLA and creatine monohydrate work independently or in combination with strength exercise to increase bone mass/density and muscle mass and function.
- To determine whether the benefits from strength exercise are related to a reduction in oxidative stress and mitochondrial DNA deletions and whether strength exercise training enhances mitochondrial function of the skeletal muscle and at the whole body level.

***Hypotheses.***

Resistance exercise training will result in:

-  strength, fat-free mass, aerobic capacity, bone mineral content, muscle fiber area, mitochondrial enzyme activity and a reduction in mitochondrial DNA deletions.
-  in the “stress pattern” from the micro-array data along with an increase in expression of mRNA species associated with the electron transport chain of the mitochondria.

CrM + CLA will result in the following adaptations that will be enhanced with strength exercise:

-  strength and functional tasks, muscle total and phosphocreatine, fat-free mass and bone mineral content and osteocalcin (bone formation).
-  oxidative stress markers and N-telopeptides (bone breakdown).

***Research Plan.***

*1. Subjects.* N = 80 healthy males and females 65 - 85 y. *2. Design/Intervention.* Randomized, double-blind study with equal allocation to 4 treatment groups: 1. Resistance training (RT) (8 months, 3dwk-1) and placebo (PL) – Group = RT + PL; 2. RT as in # 1 + CrM (5 gd-1) and CLA (3 gd-1) supplementation– Group = RT+SUPP; 3. Sedentary (8 months of home stretching (SED)) and placebo (PL) = SED; 4. SED as in # 3 + SUPP as in # 2 – Group = SED+SUPP. *3. Major outcome variables.*A. Function – muscle strength (isometric and dynamic), aerobic capacity, functional tasks; B. Anthropometry – DEXA for fat-free mass, bone mineral content and density; C. Muscle – Histology – ATPase for fiber area and type, cytochrome oxidase (COX) negative fibers, COX sub-unit II and IV and 8-OH-2deoxyguanosine by IHC; Biochemistry – electron transport activity, creatine, ATP, phosphocreatine, protein carbonyls and anti-oxidant enzymes; Molecular biology – mitochondrial DNA deletions, gene expression pattern by micro-chip technology; D. Blood – CK activity, liver and renal function tests, bone turnover markers (osteocalcin and N-telopeptide); E. Urine - 8-OH-2deoxyguanosine/creatinine.

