**PART II: (THIS SECTION MUST BE COMPLETED EVEN IF PROTOCOL IS ATTACHED)**

1. Describe the rationale and purpose of the study (250 words):

Aging is characterized by a progressive loss of muscle mass, termed, sarcopenia. Decreased strength ultimately results in an increased occurrence of falls, which are a primary cause of morbidity. Resistance exercise can partially reverse many of these changes, however, long-term compliance limits the broad application of exercise as a counter-measure for sarcopenia. We have recently shown that a dietary substance, creatine monohydrate (CrM) enhanced several of the gains following four months of exercise training in older adults (i.e., fat-free mass, knee extension strength)(Brose, et al.,  *J Gerontol A Biol Sci Med Sci.*, 58:B11-19, 2003). Another compound, conjugated linoleic acid (CLA), has been found to increase muscle mass and decrease fat mass in humans. Our purpose is to study the effects of these dietary compounds in combination with and without strength exercise training in older adults to determine the effects on muscle mass, bone mass and muscle function after one year of intervention.

1. Sample size *(Indicate how the sample size was determined and # of participants involved locally and in total for multi-centered studies)*:

Using the data from our pilot study looking at CrM and strength exercise in older adults (Brose, et al., *J Gerontol A Biol Sci Med Sci.*, 58:B11-9, 2003) we derived sample size estimates for two of the primary outcome variables:

- - 1. FFM (fat-free mass): The change in FFM for CrM after training was 1.92 kg (SD = 0.98) and for PL was 0.53 kg (SD = 0.38). The delta between the groups is 1.39 with a mean SD of 0.68. Hence using a conservative 2 tailed test, and  = 0.05 and β 0.20, the sample size comparing 2 independent groups is: n/group = 2[(Z + Zβ) SD/delta]2 = 2[(1.28 + 1.96)0.68/1.39]2 = 10.
    2. Isometric knee extension strength: The change in strength for CrM after training was 52 Nm (SD = 38) and for PL was 24 Nm (SD = 13). The delta between the groups is 28 with a mean SD of 25.5. Hence using a conservative 2 tailed test, and  = 0.05 and β 0.20, the sample size comparing 2 independent groups is: n/group = 2[(Z + Zβ) SD/delta]2 = 2[(1.28 + 1.96)20/28]2 = 21.
  1. The comparison between the effect of strength training and the sedentary group for almost every variable of interest resulted in sample size estimates of less than 10/group.

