b) Nutritional supplement (50 % of recruits; the other 50 % will consume a placebo (nested within the exercise and sedentary groups) – the supplement will consist of 3 g/d of conjugated linoleic acid and 5 g/d of creatine monohydrate for **12 months**.

1. Primary outcome(s) (***“What”*** will the study measure?):

The following measurements will be completed before (pre), at 6 months, and again at the end (+12 months) of the study:

a) Muscle and bone mass.

b) Functional capacity.

c) Knee extension strength.

d) Strength with weight training machines.

e) Muscle fiber area and creatine content.

f) Muscle oxidative capacity.

g) Aerobic power (oxygen consumption).

1. Measurements (***“How”*** will the study measure it?) and plan for data analysis:

a) Muscle and bone mass – DEXA scanning.

b) Functional capacity – stair climb, get up and go and walking test.

c) Knee extension strength – isometric dynamometery.

d) Strength with weight training machines – peak strength in 8 muscle actions.

e) Muscle fiber area and creatine content (muscle biopsy pre and post only) – ATPase staining and enzymatic biochemistry.

f) Muscle oxidative capacity (muscle biopsy pre and post only) – electron transport enzyme activity - biochemistry.

g) Aerobic power (oxygen consumption) – VO2max test + 12 lead ECG on cycle ergometer.

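### The urinary oxidative-damage marker is divided by creatinine, which the creatine supplement can itself raise, so a lower ratio on supplement need not mean less oxidative damage.

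*Protocol*

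**What the plan says.** The Research Plan (item 3, major outcome variables) ends with a single urinary outcome: "E. Urine - 8-OH-2deoxyguanosine/creatinine". The protocol as shown describes no timed collection, no absolute excretion, no other dilution correction and no check of urinary creatinine by arm.

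Section B, Part II (study interventions) states that "the supplement will consist of 3 g/d of conjugated linoleic acid and 5 g/d of creatine monohydrate". Half the participants receive it and half receive placebo, nested within the exercise and sedentary groups.

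The Hypotheses section lists, among the adaptations to the supplement, "muscle total and phosphocreatine, fat-free mass and bone mineral content and osteocalcin", and in a second line "oxidative stress markers and N-telopeptides (bone breakdown"). The direction arrows were lost when the text was read from PDF. The first line also names strength and bone formation, so it evidently means an increase. The second pairs oxidative stress with bone breakdown, so it evidently means a decrease. The same section expects these adaptations to be larger with strength exercise.

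The Research Plan also lists muscle measures of oxidative damage that do not involve creatinine: "COX sub-unit II and IV and 8-OH-2deoxyguanosine by IHC", and protein carbonyls.

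**The concern.** Dividing a urinary marker by creatinine corrects for dilution only if treatment leaves creatinine output alone. Here the intervention supplies the precursor of creatinine. The protocol's own hypotheses also expect a larger muscle creatine and phosphocreatine pool and more fat-free mass on supplement. The denominator is then a post-randomisation quantity that treatment can move.

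At stake is the meaning of a lower ratio on supplement. A rise in creatinine alone would produce it and would look like the hoped-for reduction in oxidative stress. Randomisation and blinding do not help, because treatment itself causes the shift.

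**Working it through.** The protocol gives no effect size, SD or sample size for this outcome, so there is no planned figure to reproduce.

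**Inputs from the protocol**
- Outcome: urinary 8-OH-2-deoxyguanosine divided by creatinine (Research Plan).
- Creatine monohydrate 5 g/d against placebo (Section B, Part II).
- "N = 80 healthy males and females 65 - 85 y" in four equal groups: 80/2 = 40 per supplement level. With the protocol's allowance of about 6 drop-outs, 40 − 6 = 34.
- Pilot fat-free mass: "The change in FFM for CrM after training was 1.92 kg (SD = 0.98) and for PL was 0.53 kg (SD = 0.38"). The difference is 1.92 − 0.53 = 1.39 kg.

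**Inputs assumed, because the documents give none**
- Rise r in urinary creatinine on supplement: 5% to 30%.
- SD of the change in the log ratio: 0.3 or 0.5.
- Fat-free mass: 45 to 60 kg, with creatinine output proportional to it.

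**Step 1: shift in the ratio with no true effect.** With the numerator unchanged and creatinine multiplied by (1 + r), the ratio changes by 1/(1 + r) − 1.

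| Assumed rise r | Change in ratio |
|---|---|
| 5% | 1/1.05 − 1 = −4.8% |
| 10% | 1/1.10 − 1 = −9.1% |
| 15% | 1/1.15 − 1 = −13.0% |
| 20% | 1/1.20 − 1 = −16.7% |
| 30% | 1/1.30 − 1 = −23.1% |

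Each figure is relative to a participant whose creatinine does not rise.

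**Step 2: the part due to muscle gain.** The pilot difference is 1.39/60 = 2.3% to 1.39/45 = 3.1% of fat-free mass. Trained participants on placebo gained 0.53 kg, which is 0.53/60 = 0.9% to 0.53/45 = 1.2%. On this route the trained placebo arm moves a little too, so the placebo arms cannot be taken as fixed at zero. The other route, a larger creatine pool and conversion of the ingested creatine, cannot be sized from the documents.

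**Step 3: what the shift could do to a test (illustration only).** For a two-sided 5% z-test on the log ratio, the spurious shift is ln(1 + r) and the standard error is SD × √(2/n). Take r = 10%, SD 0.3 and n = 34 per supplement level. The shift is 0.0953, the standard error is 0.3 × √(2/34) = 0.0728, and their quotient is 1.31. The chance of a significant result is then 1 − Φ(1.96 − 1.31) + Φ(−1.96 − 1.31) = 26%.

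| r | SD 0.3 | SD 0.5 |
|---|---|---|
| 5% | 10% | 7% |
| 10% | 26% | 12% |
| 15% | 48% | 21% |
| 20% | 71% | 32% |

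All exceed the nominal 5%, but the spread is wide and both inputs are assumed.

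**Step 4: which contrasts are touched.**
- Supplement against placebo takes the full shift.
- The supplement-by-exercise comparison is touched if creatinine rises by a different share in trained and sedentary supplement arms. The protocol's expectation of larger adaptations with exercise makes that plausible.
- Training against sedentary is touched only through muscle gain, because supplement is balanced across the two.

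**The case against.** The strongest reply is that nothing in the documents sizes the effect. They contain no urinary creatinine value, expected rise or SD. The only related quantity, the pilot fat-free mass difference, corresponds to about 2% to 3%. This stands: the documents support a direction, not an amount.

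The reach is also narrow. The marker is the last item of a long list in the summary. It is absent from the primary outcomes in Section B, Part II, and the sample size does not rest on it. The stated objective on oxidative stress concerns exercise, not the supplement. Muscle measures free of creatinine are planned beside it, and nothing makes the urine ratio the deciding test. All of this stands, and it limits the point to how one marker is read.

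A reader might also cite Section C, which reports no change in renal function in the four-month pilot. That is a safety statement about organ function. It gives no urinary creatinine excretion and does not show that the denominator is stable.

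Finally, specific gravity might seem a clean replacement. It is not assured: excreted creatine adds solute to urine on supplement and can raise specific gravity too.

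**Conclusion.** The point holds as a bias of known direction and unknown size. As defined, the ratio can fall on supplement with no change in oxidative damage. Assumed creatinine rises of 5% to 30% would lower it by 4.8% to 23.1% relative to no rise. The direction rests on creatine being the precursor of creatinine and on reading the lost arrows in the Hypotheses as an increase in muscle creatine and fat-free mass and a decrease in oxidative stress.

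A reader might infer three stronger things that the documents do not support:
- **A false-positive rate can be stated.** It cannot, because both the creatinine rise and the SD are assumed.
- **Only the supplement arms move, with the placebo arms unchanged.** Muscle gain can shift the trained placebo arm slightly as well.
- **The trial's test of oxidative stress fails as a whole.** It does not. The muscle measures are unaffected, and the training contrast is touched only through muscle gain.

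The point is worth acting on because the change is cheap and alters what a lower ratio on supplement may be taken to show.

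**What to change.** - Name the planned muscle measures (8-OH-2-deoxyguanosine by IHC, and protein carbonyls) as the test of the supplement effect on oxidative stress.
- Keep the urinary ratio as descriptive for the supplement contrast and for the supplement-by-exercise comparison.
- Report urinary creatinine and unadjusted 8-OH-2-deoxyguanosine separately by arm. Both are already needed to form the ratio, so no new assay is required. The unadjusted value varies with urine dilution, so it serves interpretation and should not become a replacement test.
- Specific gravity may be added only as a sensitivity analysis, for the reason given above. It would need an extra reading, and the protocol as shown does not describe how urine is collected.

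The cost is a change in the wording of one outcome and two extra rows in a table. The downside is that one urinary marker loses confirmatory standing for the supplement contrast.

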(including patents or stocks) in this research study? [ ] YES [X] NO

1. Receive an honorarium or other benefits from the sponsor (apart from fees

for service)? [ ] YES [X ] NO

- 1. If the answer is YES to any of the above, please describe and explain how that conflict

is being managed to ensure that participant rights and welfare are not affected. [ ] Attached

1. Sponsor Agreement:

*(Note: Agreements must be reviewed and signed by authorized institutional officials.)*

Will there be a signed contract/agreement with the sponsor related to this study? [ ] YES [ ] NO

If YES, will it in any way limit your access to the research data, or limit your right to

publish the study results? [ ] YES [ ] NO

If YES, please explain.

1. New Investigational Drug or Device, and Off-label Use:

Is this a clinical study involving a new investigational drug(s) or device, or a drug or

device used for an indication outside the parameters of the approved Health Canada

Notice of Compliance (NOC) or Drug Identification Number (DIN) application or Medical

Device Licence, as applicable? [ ] YES [ X] NO

If YES, has the Sponsor or the Institution/Investigator initiating the study filed a Clinical

Trial application or Medical Device Licence Application with Health Canada? [ ] YES [ ] NO

If YES, attach a copy of the Health Canada “No Objection” letter.

*(Note: Study may NOT commence without Health Canada approval.)*

10. (a) Does this study involve an infectious agent? [ ] YES [ X] NO

If YES, attach approval letter from Infection Control.

(b) Does this study involve a biosafety hazard? [ ] YES [ X] NO

If YES, attach approval letter from the Biosafety Committee.

(c) Does this study include genetic testing or storage of tissues/samples? [ ] YES [X] NO

If YES, attach a separate consent form addressing the special concerns

related to genetic testing or storage of tissues/samples. *(Note: See Informed Consent Checklist attached.)*

**SECTION B – DESCRIPTION OF PROPOSED RESEARCH**

**PART I: BRIEF SUMMARY (4 – 5 lines) OF PROPOSED RESEARCH WRITTEN IN SIMPLE ENGLISH APPROPRIATE FOR LAY REVIEWERS (Do not use jargon or medical short forms). USE THE FOLLOWING HEADINGS;**

**(i) Main Research Question(s)** – Do the dietary supplements creatine monohydrate and conjugated linoleic acid enhance the benefits of strength exercise training in older adults and do they increase muscle function, mass and bone density on their own?

**(ii) Why is this research important? –** Muscle weakness and bone loss are major causes of disability in older adults and strategies that enhance muscle and bone mass should have significant beneficial effects on health and mobility of older adults.

**(iii) What is being studied? –** Muscle strength, aerobic fitness, bone mass, functional capacity will be determined before and after one year of supervised weight training in older adults as compared to a cohort of adults who do not exercise. Within each group, half will be taking the dietary supplements, creatine monohydrate and conjugated linoleic acid.

**PART II: (THIS SECTION MUST BE COMPLETED EVEN IF PROTOCOL IS ATTACHED)**

1. Describe the rationale and purpose of the study (250 words):

Aging is characterized by a progressive loss of muscle mass, termed, sarcopenia. Decreased strength ultimately results in an increased occurrence of falls, which are a primary cause of morbidity. Resistance exercise can partially reverse many of these changes, however, long-term compliance limits the broad application of exercise as a counter-measure for sarcopenia. We have recently shown that a dietary substance, creatine monohydrate (CrM) enhanced several of the gains following four months of exercise training in older adults (i.e., fat-free mass, knee extension strength)(Brose, et al.,  *J Gerontol A Biol Sci Med Sci.*, 58:B11-19, 2003). Another compound, conjugated linoleic acid (CLA), has been found to increase muscle mass and decrease fat mass in humans. Our purpose is to study the effects of these dietary compounds in combination with and without strength exercise training in older adults to determine the effects on muscle mass, bone mass and muscle function after one year of intervention.

1. Sample size *(Indicate how the sample size was determined and # of participants involved locally and in total for multi-centered studies)*:

Using the data from our pilot study looking at CrM and strength exercise in older adults (Brose, et al., *J Gerontol A Biol Sci Med Sci.*, 58:B11-9, 2003) we derived sample size estimates for two of the primary outcome variables:

- - 1. FFM (fat-free mass): The change in FFM for CrM after training was 1.92 kg (SD = 0.98) and for PL was 0.53 kg (SD = 0.38). The delta between the groups is 1.39 with a mean SD of 0.68. Hence using a conservative 2 tailed test, and  = 0.05 and β 0.20, the sample size comparing 2 independent groups is: n/group = 2[(Z + Zβ) SD/delta]2 = 2[(1.28 + 1.96)0.68/1.39]2 = 10.
    2. Isometric knee extension strength: The change in strength for CrM after training was 52 Nm (SD = 38) and for PL was 24 Nm (SD = 13). The delta between the groups is 28 with a mean SD of 25.5. Hence using a conservative 2 tailed test, and  = 0.05 and β 0.20, the sample size comparing 2 independent groups is: n/group = 2[(Z + Zβ) SD/delta]2 = 2[(1.28 + 1.96)20/28]2 = 21.
  1. The comparison between the effect of strength training and the sedentary group for almost every variable of interest resulted in sample size estimates of less than 10/group.
  2. In our pilot study we had a drop-out rate of 7 %, and if we assume a drop-out rate of twice this (~ 6/group), we should retain 34 people at each of the two centers with 34 in RT and 34 on the combined supplement.

1. Design/Methodology:

Participants who are deemed eligible to participate will be randomly allocated into one of four groups. The allocation will be based upon an expected equal recruitment at the London (total = 40) and Hamilton (total = 40) sites and there will be 10 independent blocks of 4 randomly distributed interventions at each site (20 allocated to strength exercise (10 = + supplement; 10 = no supplement) and 20 allocated to no exercise (10 = + supplement; 10 = no supplement)) with an equal distribution:

1. Resistance training (RT) (12 months, 3dwk-1) and placebo (PL) – Group = RT + PL.

2. RT as in # 1 + CrM (5 gd-1) and CLA (3 gd-1) supplementation (SUPP) – Group = RT+SUPP.

3. Sedentary (12 months of home stretching (SED)) and placebo (PL) = SED.

4. SED as in # 3 + SUPP as in # 2 – Group = SED+SUPP.

1. Setting (e.g. outpatient, ICU, community):

The participants will be healthy ambulatory community dwelling men and women over the age of 65 y.

a. Exercise testing – Rm 4U18 and 2F MUMC (Neuromuscular research testing area – [name]).

b. Exercise training – Tue and Thur. – Ivor Wynne Center exercise center.

1. (a) Brief description of participants:

Men and women over the age of 65 y and less than 85 y who are living independently in the community with no contra-indications to exercise testing or training will be recruited.

(b) Are there any age, ethnicity, language, gender or race-related inclusion or exclusion criteria? [ ] YES [ X ] NO

If YES, please justify:

We plan to recruit equal numbers of men and women.

1. Study interventions:

a) Exercise training (50 % of recruits; other 50 % will continue with their usual routine) – participants will perform supervised strength/resistance exercise three times a week (Tue/Thur) for **12 months** using a machine based whole body exercise program that we have shown previously to be safe and effective (Brose, et al.,  *J Gerontol A Biol Sci Med Sci.*, 58:B11-9, 2003). Subjects will also perform a home based exercise routine on Saturday with rubber bands and resistance exercises not requiring weights (i.e., sit-ups).

b) Nutritional supplement (50 % of recruits; the other 50 % will consume a placebo (nested within the exercise and sedentary groups) – the supplement will consist of 3 g/d of conjugated linoleic acid and 5 g/d of creatine monohydrate for **12 months**.

1. Primary outcome(s) (***“What”*** will the study measure?):

The following measurements will be completed before (pre), at 6 months, and again at the end (+12 months) of the study:

a) Muscle and bone mass.

b) Functional capacity.

c) Knee extension strength.

d) Strength with weight training machines.

e) Muscle fiber area and creatine content.

f) Muscle oxidative capacity.

g) Aerobic power (oxygen consumption).

1. Measurements (***“How”*** will the study measure it?) and plan for data analysis:

a) Muscle and bone mass – DEXA scanning.

b) Functional capacity – stair climb, get up and go and walking test.

c) Knee extension strength – isometric dynamometery.

d) Strength with weight training machines – peak strength in 8 muscle actions.

e) Muscle fiber area and creatine content (muscle biopsy pre and post only) – ATPase staining and enzymatic biochemistry.

f) Muscle oxidative capacity (muscle biopsy pre and post only) – electron transport enzyme activity - biochemistry.

g) Aerobic power (oxygen consumption) – VO2max test + 12 lead ECG on cycle ergometer.

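### Both sample-size lines are wrong as written: the printed formulas give 5.02 and 10.71 per group, not 10 and 21, and their z-value and one SD contradict the stated inputs

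*Protocol*

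**What the plan says.** In the Protocol, Section B, Part II, Sample size, pilot data on creatine versus placebo after training are used to size two primary outcomes. The test is described as two-tailed ("using a conservative 2 tailed test") with error rates of "0.05 and β 0.20". The formula is n/group = 2[(Zα + Zβ) SD/delta]², where the last 2 is a superscript lost in text extraction.

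- **FFM.** The pilot changes are 1.92 kg (SD 0.98) on creatine and 0.53 kg (SD 0.38) on placebo, so delta is 1.39 and the mean SD 0.68. The line ends "2[(1.28 + 1.96)0.68/1.39]2 = 10".
- **Isometric knee extension.** The pilot changes are 52 Nm (SD 38) and 24 Nm (SD 13). The text says "The delta between the groups is 28 with a mean SD of 25.5", and the line then ends "2[(1.28 + 1.96)20/28]2 = 21".

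The same section states, without a calculation, that training versus sedentary needs fewer than 10 per group. It also assumes twice the pilot drop-out of 7%, put at about 6 per group with 34 retained. The Research Plan and Design/Methodology give N = 80 in four equal groups, that is 20 per cell.

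**The concern.** The form asks how the sample size was determined, and these two lines are the only worked calculations that answer it. Neither result follows from the expression printed beside it. The z-value belongs to a different power from the one stated, and one SD differs from the value given a sentence earlier. A reader cannot tell whether 80% or 90% power was planned, or how many participants each comparison needs. The printed 21 also looks plausible only because the errors partly cancel.

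**Working it through.** **Inputs** (Protocol, Section B, Part II, Sample size): two-sided α = 0.05 (z = 1.96); stated β = 0.20 (z = 0.84); printed z = 1.28; FFM delta 1.39 kg with SDs 0.98 and 0.38; knee-extension delta 28 Nm with SDs 38 and 13. Planned cell size: 80/4 = 20.

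**1. The lines exactly as printed**
- FFM: 2 × (3.24 × 0.68/1.39)² = 5.02. The protocol prints 10.
- Knee extension: 2 × (3.24 × 20/28)² = 10.71. The protocol prints 21.
- Twice these values is 10.05 and 21.42, which match 10 and 21 when rounded down. A total over two groups labelled as n per group would explain both figures, but this is an inference. No variant tried reproduces both figures as n per group.

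**2. The z-value.** β = 0.20 needs 0.84, so the sum is 2.80. The printed 1.28 belongs to β = 0.10, with sum 3.24.

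**3. The SD.** (38 + 13)/2 = 25.5, as the text says. Nothing in the document gives 20. Using it lowers n by a factor of (25.5/20)² = 1.63.

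**4. The stated inputs applied consistently (β = 0.20, mean SDs)**
- FFM: 2 × (2.80 × 0.68/1.39)² = 3.75, so 4 per group.
- Knee extension: 2 × (2.80 × 25.5/28)² = 13.005, so 14 per group.

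The printed 10 and 21 are higher than both.

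**5. Averaging unequal SDs.** With equal arms, the variance of the difference depends on the mean of the squared SDs.
- FFM: √((0.98² + 0.38²)/2) = 0.743 kg, against 0.68.
- Knee extension: √((38² + 13²)/2) = 28.4 Nm, against 25.5. This raises n by (28.4/25.5)² = 1.24.

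**6. Required n per group with the root-mean-square SDs**

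| Outcome | Power | Normal formula | t-test |
|---|---|---|---|
| FFM | 80% | 4.48 → 5 | 5.63 → 6 |
| FFM | 90% | 6.00 → 7 (just above 6) | 7.12 → 8 |
| Knee extension | 80% | 16.13 → 17 | 17.16 → 18 |
| Knee extension | 90% | 21.60 → 22 | 22.62 → 23 |

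**7. Knee-extension power (two-sided t-test, delta 28)**

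| n per cell | SD 25.5 | SD 28.4 |
|---|---|---|
| 20 (planned) | 92% | 86% |
| 17 (20 × 0.86 = 17.2, drop-out 2 × 7% spread evenly) | 87% | 79.6% |

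**8. What a group means.** The drop-out of about 6 per group fits 14% of 40 (5.6), leaving 34. That sentence therefore appears to count factorial margins of 40, while the pilot contrast (creatine versus placebo, both trained) corresponds to two cells of 20. At 34 per margin and SD 28.4, knee-extension power would be 98% if the same effect held across the margin.

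**The case against.** The best defence is that nothing in the design is harmed. The printed figures exceed what the stated β and SDs require (10 against 4, 21 against 14), and at 20 per cell the power for knee extension is above 80% with either supported SD. That stands, and it limits the point to the justification.

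Three further objections also hold. The mean SD is openly labelled as such, so averaging is a weaker approximation and not a contradiction like the other items. The doubling explanation is not documented. The two lines are not the only planning figures, since the training comparison and the drop-out allowance are also given.

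A reader might infer that the trial is underpowered, since 21 per group exceeds the 20 per cell. The documents do not support that, because 21 is itself the miscalculated figure and does not follow from the stated inputs. A reader might also take 1.28 as proof that 90% power was planned. The text says β = 0.20 in both lines, so the document is inconsistent on power and does not settle it.

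None of this repairs the printed lines.

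**Conclusion.** The point holds as an error of arithmetic and consistency. Both results are about twice what their own expressions give, the z-value contradicts the stated β, and the SD of 20 contradicts the stated 25.5. The use of mean SDs is a lesser matter of method that makes n too small.

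The net effect is conservative against the stated inputs, and no shortfall against 80% power is shown at 20 per cell. The margin for knee extension is thin, however. With SD 28.4 and 17 retained per cell, power is about 80% (79.6%), and 90% is out of reach even with all 20.

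These figures assume that the pilot creatine effect and SDs carry over to the combined supplement, a two-sided t-test at 0.05, and drop-out spread evenly over the cells.

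**What to change.** Rewrite the two lines in Section B, Part II, Sample size:

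- Keep β = 0.20 and use z = 0.84.
- Use the root-mean-square SDs, 0.743 kg and 28.4 Nm.
- Report a true per-group n: 6 for FFM and 18 for isometric knee extension on a t-test basis (5 and 17 by the normal formula, if that is kept and named).
- Delete the SD of 20 and the results 10 and 21.
- Say whether a group is one of the four cells (20 each) or a factorial margin (40 each), and use that meaning in the drop-out sentence too.
- State the knee-extension power at SD 28.4: 86% with 20 per cell, and about 80% with 17 per cell if the 14% drop-out is spread evenly.

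If 90% power was intended, knee extension needs 23 per group (t-test, SD 28.4). Cells of 20 do not provide this, so 90% should not be claimed for the cell comparison.

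The cost is protocol wording only. At the stated 80% power no added enrolment is needed.

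### The retained 34 is a factorial margin: the supplement contrast that was sized keeps about 17 per group, and the stated 21 per group is miscalculated

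*Protocol*

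**What the plan says.** All references are to the Protocol.

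- **Sample size (Section B, Part II).** The knee extension inputs are pilot changes in trained people: "The change in strength for CrM after training was 52 Nm (SD = 38) and for PL was 24 Nm (SD = 13". The difference is 28 Nm and the mean SD is given as 25.5. The test is two-sided, with "0.05 and β 0.20, the sample size comparing 2 independent groups is" followed by the expression "2[(1.28 + 1.96)20/28]2 = 21".
- **Drop-out allowance, same section.** The pilot drop-out of 7% is doubled and rendered as about 6 per group. The conclusion is that "we should retain 34 people at each of the two centers with 34 in RT and 34 on the combined supplement".
- **Design/Methodology, same part.** Each of two sites has 40 participants, with "20 allocated to strength exercise (10 = + supplement; 10 = no supplement") and the same split among those who do not exercise. That makes four groups of 20.
- **Hypotheses.** "CrM + CLA will result in the following adaptations that will be enhanced with strength exercise".
- **Main research question (Section B, Part I).** It asks whether the supplements add to training and also whether they work alone.

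**The concern.** The word group changes meaning within one section. In the formula it is one arm of a two-arm comparison of creatine and placebo in trained people. In the drop-out allowance it is half the trial: everyone who trains, or everyone on supplement. A reader who sets 34 beside 21 will think there is a comfortable reserve. For the comparison from which the 28 Nm was taken, the stated 21 exceeds even the 20 randomised.

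The margin of 34 does not measure the same thing. It averages the supplement effect over trained and sedentary people, and the protocol gives no effect size for sedentary people. If the supplement does less without training, as the hypothesis implies, the margin tests a smaller effect than the one used for sizing. The interaction, which is the formal test of enhancement by exercise, has no sample size. A diluted main effect or an inconclusive interaction could then be read as evidence against the supplement.

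**Working it through.** **1. Counts.**
- Per margin: 40 × 0.14 = 5.6 lost (the protocol's figure of about 6), and 40 − 6 = 34 retained.
- Per randomised group: 20 × 0.14 = 2.8 lost (about 3), and 20 × 0.86 = 17.2 retained (about 17).
- The protocol's 6 and 34 reproduce only with a denominator of 40, and 34/17 = 2.

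**2. The stated 21.** The printed formula is n per group = 2[(Zα + Zβ) × SD/delta]².
- As printed: 2[(1.28 + 1.96) × 20/28]² = 10.7, not 21.
- The expression uses SD 20, where the text gives 25.5. It uses 1.28 (90% power), where β = 0.20 needs 0.84.
- Twice 10.7 is 21.4. The companion fat-free mass expression gives 5.02, and twice that is 10.05 against a stated 10. Both printed results therefore look like two-group totals labelled per group. This is an inference.

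**3. Corrected requirement** (two-sided 0.05, 80% power, delta 28 Nm).
- SD 25.5: 2[(0.8416 + 1.96) × 25.5/28]² = 13.02, so 14 per group; 15 by noncentral t.
- Root-mean-square SD, √[(38² + 13²)/2] = 28.4: 2[(0.8416 + 1.96) × 28.4/28]² = 16.15, so 17 per group; 18 by noncentral t.

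**4. Power of RT+SUPP versus RT+PL with 17 per group, 28 Nm.**

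| Method | Power |
|---|---|
| Noncentral t, SD 25.5 | 87% |
| Noncentral t, SD 28.4 | 80% |
| Welch test, simulated, SDs 38 and 13 | 78% |

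For fat-free mass, 17 per group gives over 99% power for the pilot effect of 1.39 kg.

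**5. Supplement margin, 34 versus 34.** The sedentary effect is not in the protocol, so it is an assumption: a fraction f of 28 Nm. The average effect is then 28(1 + f)/2. A common SD is also assumed.

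| f | Average effect | Power, SD 25.5 | Power, SD 28.4 |
|---|---|---|---|
| 1 | 28 Nm | 99% | 98% |
| 0.5 | 21 Nm | 92% | 85% |
| 0 | 14 Nm | 61% | 52% |

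**6. Interaction, 17 per cell.** With a common SD, the standard error is 2 × SD/√17 on 64 df.
- Interaction of 28 Nm (sedentary effect zero): 61% (SD 25.5) or 52% (SD 28.4).
- Interaction of 14 Nm (sedentary effect half): 20% or 17%.
- If instead both sedentary cells have SD 13 (an assumption) and the trained cells 38 and 13, the standard error is √[(38² + 3 × 13²)/17] = 10.7. Power for 28 Nm is then about 71% with Satterthwaite df and 73% with pooled variance.

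**The case against.** The strongest reply is that nothing is short. The 21 is an arithmetic slip, β = 0.20 is stated in words, and 17 completers give about the declared power for knee extension and ample power for fat-free mass. **This stands.** A reader might infer that the trial is underpowered, and that holding 21 per group after 14% loss needs 21/0.86 = 24.4, so 25 per group and 100 in total. The documents do not support that, because 21 is not a sound requirement.

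A second reply is that a margin is a legitimate analysis. **This also stands.** A reader might infer that the hypothesised interaction invalidates the margin. It does not: the margin still validly tests the average supplement effect. The Hypotheses expect a benefit that exercise increases, not one that is absent without exercise, and with half the effect in sedentary people the margin has 85% to 92% power. The effect is diluted, and it does not answer the within-training question.

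A third reply is that the interaction power depends on SDs that the protocol does not give for sedentary people. **This stands.** A reader might infer a ceiling of 50% to 60%, but that rests on a common SD.

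Two further points have partial force. The section on withdrawals keeps later drop-outs in an intention-to-treat analysis, so 17 is a completer count; but so is the protocol's 34, and the comparison is like with like. The protocol also never says that 34 satisfies the 21; that is the natural reading, not a statement. Contrasts and interaction reporting can be left to an analysis plan. The retained number and the 21, however, are stated in this document, and they are wrong for the contrast that was sized.

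**Conclusion.** The concern holds as a misstatement in the sample size justification, not as a shortage of participants. The retained number for the sized supplement contrast is about 17 per group. The 34 is a margin and overstates it twofold. The stated 21 is delivered neither at randomisation (20) nor after drop-out (17), and it does not follow from its own expression. Computed from the declared inputs, the requirement is about 14 to 18 per group, so 17 is roughly adequate, with 78% to 87% power.

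This rests on the pilot effect of 28 Nm carrying over to the combined supplement, on SDs between 25.5 and 28.4 (or 38 and 13 taken separately), and on 14% drop-out spread evenly over the four groups. The margin tests 28 Nm only if the supplement works equally in sedentary people. The trial was not sized for the interaction, and any power quoted for it depends on the sedentary effect and SD that are assumed.

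**What to change.** Amend the sample size text, with no increase in N:

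1. Identify RT+SUPP versus RT+PL as the contrast that was sized.
2. Replace the loss of about 6 per group and the retained 34 with about 3 lost and 17 retained per randomised group. Give 34 only as the margin count, labelled as such.
3. Replace the 21 with a figure computed from the declared inputs, using one stated SD and the Z value for β = 0.20. Recompute the companion fat-free mass figure in the same way.
4. Restate knee extension power at 17 per group as about 80%: 78% (Welch, SDs 38 and 13), 80% (SD 28.4), 87% (SD 25.5).
5. State that the trial was not sized for the supplement-by-exercise interaction. If a power is quoted, give its assumptions with it: 52% to 61% for 28 Nm with a common SD of 28.4 to 25.5; about 71% to 73% for 28 Nm if the sedentary SDs are 13; 17% to 20% for 14 Nm with a common SD.

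The cost is a few sentences and a less favourable stated retained number.
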